#### Pain, Function, and Quality of Life Assessment

Knee Injury and Osteoarthritis Outcome Score (KOOS) is a validated questionnaire used within the orthopaedic literature to assess the effect of interventions on the perceived severity of knee OA [12] and has previously been reported in the GAE literature [5, 6]. KOOS is intended to be used over short- and long-term time intervals, to assess changes from week to week induced by treatment (medication, operation, physical therapy) or over years following a primary injury or OA. KOOS is responsive to change following non-surgical and surgical interventions (Online Appendix A). The primary outcome measure for the current study is improvement in the 4 Knee Injury and OA Outcome Score subscales (KOOS_4_), covering pain, symptoms, activities of daily living, and quality of life at 6 months in patients with mild to moderate knee OA. Sports and recreation were the most inconsistently reported measure from Genesis, hence its exclusion [6]. Total KOOS will be analysed as a secondary endpoint. The Minimum Clinically Important Difference (MCID) will be used to define clinical success. A 10-point increase in KOOS scores will be used to define the MCID based on the work by Roos [6, 12]. The proportion of participants achieving the MCID at 6 months will be compared between the GAE and sham treatment for all 5 KOOS subscales. In addition to the quality of life assessment from the KOOS questionnaire, the EuroQoL-5D (EQ-5D-3L) will be completed.

A visual analogue scale (0–100) will also be used to assess pain in the affected knee. This will be performed at baseline, with participants with a VAS < 50 excluded.

Analgesia use will not be controlled throughout the study. Participants will be asked if they are taking analgesia specific to their knee pain at follow-up, enabling longitudinal trends in analgesia use to be compared to treatment response following GAE or the sham procedures.

Pain, function, analgesia, and quality of life assessment data will be prospectively collected using a purposely designed Electronic Data Capture System (EDC).

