### Secondary Outcomes with Hypothesis Testing

Clinical success: Proportion of subjects reporting ≥ 10-point improvement in KOOS scores, where a 10-point change from baseline is defined as the minimum clinically important difference (MCID) at 6 months post-randomisation.Pain relief: VAS change through 6 months post-randomisation.

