### Secondary Outcomes with Descriptive Statistics

*OA symptom relief* Proportion of subjects reporting ≥ 10-point improvement in KOOS scores for each of the 5 KOOS subscales at 6 months post-randomisation*Safety* The proportion of subjects experiencing relevant adverse events that are possibly, probably, or definitely related to treatment received, GAE or Sham, from randomization through 6 months post randomization will be summarized by severity and compared between GAE and sham arms [15].*Synovial hypertrophy and neo-vascularisation* Whole-Organ Magnetic Resonance Imaging Score (WORMS) [14] at 6 months post-randomisation*Neural and behavioural indicators of predisposition to central facilitation of pain* Three assessments quantifying (1) sensory pain profiles, (2) psychological profiles, (3) individual differences in neurochemistry and functional connectivity, with psychological profile quantified and calibrated for pain sensitivity and modulatory ability at 6 months post-randomisation*Quality of life* Pre- and post-intervention EuroQoL-5D (EQ-5D-3L) for GAE versus non-crossover sham participants at 6 months post-randomisation*Patient-reported acceptability of study procedure* Questionnaire 1 week after GAE

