### Sample Size

Alongside a sham surgery placebo arm, a high-quality systematic review of surgical RCTs was used as a suitable benchmark to inform the sample size and power calculation [16, 17]. With a 0–100 scale for the primary endpoint of KOOS_4_, assuming a 1:1 randomisation, a mean difference of 6.4 (i.e. effect size) between GAE and sham treatments, a common standard deviation of 10 (a Cohen’s D of 0.64), an alpha error of 2-sided 0.05, and a power of 0.85, the 2-arm total sample size requirement is 88 subjects (44 each arm) by Normal approximation. Allowing for a participant dropout rate of 20%, the enrolment goal is 110 participants, approximately 55 in each study arm. Study activities (Table 2) will take place at a single academic centre in the UK.

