### Statistics

#### Endpoints

All efficacy analyses will be performed on the intention-to-treat population (all randomised subjects).

Change of KOOS4 (mean of pain, symptoms, activities of daily living, and quality of life subscores) will be compared between GAE and sham treatment arms in an ANCOVA model (vs. treatment arm indicator and baseline KOOS4 score). A secondary ANCOVA model will further include pain medication taken through 6 months.

The proportion of subjects achieving the MCID (10 points) will be compared between the sham treatment and GAE arms by Fisher’s exact test for all 5 KOOS subscales.

Subjects’ 6-month VAS will be compared between GAE and sham treatment arms in an ANCOVA model (vs. treatment arm and baseline pain score). Should the VAS be generally low, score will be dichotomised to with (> 0) or without pain (= 0), and a logistic regression analysis will be performed.

All 5 subscales of the KOOS questionnaire will be analysed at 6 months follow-up. Each sub-scale will be compared between the GAE and sham arms in an ANCOVA model (vs. treatment arm indicator and the baseline sub-scale score). An additional analysis will further include investigational site in the model.

All remaining endpoints will be descriptive, and formal hypothesis testing will not be performed. Continuous data will be reported as mean, standard deviations, median, minimum, and maximum. Categorical data will be summarised as frequency and proportions.

The proportions of subjects experiencing relevant adverse events that are possibly, probably, or definitely related to treatment received, GAE or sham treatment, from randomisation through 6 months post-randomisation will be summarised by severity and compared between GAE and sham arms.

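### The outcome lists and the statistics section disagree on which KOOS responder outcome is tested, and clinical success has no test on a single named score

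*Protocol article*

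**What the plan says.** Four parts of the protocol article bear on this.

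- **Secondary Outcomes with Hypothesis Testing** has two entries, clinical success and VAS. Clinical success is the proportion with at least a 10-point "improvement in KOOS scores, where a 10-point change from baseline is defined as the minimum clinically important difference". No score (KOOS4, total KOOS or a subscale) is named.
- **Secondary Outcomes with Descriptive Statistics** has a separate entry, OA symptom relief: the proportion with at least a 10-point "improvement in KOOS scores for each of the 5 KOOS subscales at 6 months post-randomisation".
- **Statistics, Endpoints** gives one responder analysis, Fisher's "exact test for all 5 KOOS subscales". It then adds, for mean scores, "Each sub-scale will be compared between the GAE and sham arms in an ANCOVA model", and says that whatever endpoints remain are descriptive and not formally tested.
- **Pain, Function, and Quality of Life Assessment** ties clinical success to a 10-point MCID, again without naming a score. It says the MCID proportion will be compared between arms on all five subscales, and also that "Total KOOS will be analysed as a secondary endpoint".

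**The concern.** The tier labels and the analyses do not match. The descriptive responder outcome is the one given p-values. The tested responder outcome has no analysis on one named score. No passage says whether one, most or all of the five subscale tests must succeed.

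Two smaller mismatches sit beside this. The 6-month subscale ANCOVAs correspond to no entry in either secondary list. Total KOOS is called a secondary endpoint but is in neither list.

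Responder status is how this trial defines clinical success, so the result is likely to be quoted. If the score is settled only after the 6-month unblinding, a reader cannot tell a planned claim from one chosen because it came out well.

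**Working it through.** **The passages side by side**

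| Place | Responder outcome | Status |
|---|---|---|
| Tested secondary list | one outcome, score not named | tested |
| Descriptive secondary list | five subscale proportions | descriptive |
| Pain, Function, and Quality of Life Assessment | success on an unnamed score, then five subscale proportions | compared between arms |
| Endpoints | five subscale proportions | Fisher's exact test |

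There are two ways to reconcile these.

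1. *Clinical success means the five proportions.* The descriptive list then repeats a tested outcome under the opposite label, and one outcome has five p-values with no decision rule.
2. *Clinical success means one overall score (KOOS4 or total KOOS).* It then has no stated analysis, the sentence on remaining endpoints would leave it untested, and the Fisher tests fall on an outcome listed as descriptive.

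Both readings require a change to the text.

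**The plan's own figure**

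Inputs from Sample Size: "a mean difference of 6.4 (i.e. effect size) between GAE and sham treatments", SD 10, and "an alpha error of 2-sided 0.05, and a power of 0.85".

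n per arm = 2 × (1.960 + 1.036)² × (10/6.4)² = 2 × 8.978 × 2.441 = 43.8, rounded up to 44. The total is 88, and 88/0.80 = 110 enrolled. The stated sizes reproduce.

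**Error rate if any one of five tests were enough**

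The article states alpha only for the primary. Two-sided 0.05 per test is assumed here.

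- Five independent tests at their full nominal level: 1 − 0.95⁵ = 0.226. The bound under any dependence is 5 × 0.05 = 0.25.
- Fisher's test is conservative and the subscales are probably correlated, so the realistic figure is lower. The article gives neither correlations nor responder rates, so both are assumed. In the simulation each participant has five equally correlated latent normal scores, cut at a responder rate common to both arms. Each subscale is tested by two-sided Fisher at 0.05, with 20,000 runs per cell.

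Chance that at least one of the five is significant:

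| Correlation | 44/arm, 30% respond | 44/arm, 50% | 55/arm, 30% | 55/arm, 50% |
|---|---|---|---|---|
| 0 | 13.4% | 12.3% | 14.7% | 13.2% |
| 0.5 | 12.5% | 11.2% | 13.4% | 11.9% |
| 0.7 | 10.9% | 9.9% | 12.1% | 11.2% |
| 0.8 | 10.4% | 9.3% | 11.3% | 10.5% |

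A single Fisher test in the same runs rejected in 2.5% to 3.3%. The any-of-five rate is thus 9% to 15%, roughly three to five times that of one Fisher test.

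**Power, which matters only for ordering the tests**

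Take the planned effect (6.4, SD 10), 44 per arm, and an assumed mean sham change of 2, 5 or 8. One Fisher responder test then has 54% to 57% power, against about 84% for a t-test on the continuous change.

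**The case against.** The strongest defence is that the assessment section and Endpoints agree with each other. Both compare the MCID proportion on all five subscales, so the tested outcome may simply be those five proportions, with the descriptive entry misplaced. That reading is coherent, but it concedes the contradiction and still leaves five p-values for one outcome.

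It is also fair that a multiplicity scheme for secondary outcomes often sits in an analysis plan, which is not shown here. Its absence alone would be no finding. What stands is that an analysis plan could not resolve this without overriding one part of the article.

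A reader might infer more than the text supports:

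- *That success may be claimed from any one subscale.* No passage says so. The 9% to 15% is conditional on such a rule.
- *That the subscale ANCOVAs should be counted too, raising the error rate further.* They are not responder tests, and nothing lets them support clinical success.
- *That a promised KOOS4 responder test was left out.* The article never promises one. KOOS4 is a sensible choice of score, not a missing commitment.
- *That low responder power is a fault.* The sample size is justified for the primary only.
- *That testing sport and recreation contradicts its exclusion from KOOS4.* It was left out of the composite, and the same section plans the five-subscale comparison.

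**Conclusion.** The point holds as an internal contradiction about a secondary outcome. The tested tier, the descriptive tier and Endpoints cannot all be followed, and clinical success has no single named score with a single test. The placement of the subscale ANCOVAs and of total KOOS is unresolved as well.

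The size is conditional. Under an any-of-five claim, and under the correlations, responder rates and arm sizes assumed above, the false-positive chance is about 9% to 15% instead of about 2.5% to 3%. The primary KOOS4 ANCOVA and the 88/110 sample size do not depend on any of this. It should be fixed, but it does not threaten the main conclusion.

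**What to change.** 1. Define clinical success as an improvement of at least 10 points on one named score at 6 months. KOOS4 matches the primary. Test it once, by the planned Fisher's test or by logistic regression on arm and baseline score. Either is acceptable.
2. Make the assessment section, the descriptive list and Endpoints agree that the five subscale proportions and the subscale ANCOVAs are reported as estimates with 95% confidence intervals and no significance claim. If they are to stay tested, list them as tested and state a multiplicity rule. Holm across the five proportions would use thresholds from 0.05/5 = 0.01 for the smallest p-value up to 0.05 for the largest.
3. Add total KOOS to the descriptive list.
4. Do not make the VAS test depend on the responder test. At 54% to 57% power, that gate would close in 43% to 46% of trials under the planned effect. If error control across the two tested secondaries is wanted, use Holm (0.025, then 0.05) or test VAS first.

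The cost is a wording change in the protocol and analysis plan, made before unblinded data are seen. No participants are added. What is given up is the ability to claim significance on a single subscale.

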### Interventions

#### GAE/Sham Procedure

Participants will be randomly allocated (1:1) to GAE or sham treatment using a computational generator created using code in Excel. The generator is maintained on a password protected research server. On the procedure day, an unblinded trained radiographer will inform the staff performing the study procedure of the participant’s allocation. At the 1-month and 6-month visits, participants will be asked which group they believed they were allocated to in order to assess accuracy of blinding. At 6 months post-randomisation, the participants and the study team will be unblinded. 6 months was chosen for unblinding as we know from prior studies that the median time for participants to reach maximum benefit from GAE is at least 3-months [10]. More importantly, we need a time period long enough to formally capture the placebo effect, whilst considering a time reasonable for participants to remain in the sham arm to maximise study recruitment, and minimise drop out.

GAE will be performed using 100-micron Embozene™ embolisation particles and following previously described methods for GAE [6]. The pathological embolisation target of the genicular arteries that supply the diseased portion of the knee is determined by patient symptoms and classical hyperaemic blush on angiography. All genicular arteries pertaining to the patients pain/synovitis demonstrated on preceeding contrast-enhanced MRI will be interrogated. Cone-beam CT (Allura FD20, Philips, Amsterdam) with contrast (6 ml of 100% contrast, 0.3 ml/s, 6 s delay) will be performed to confirm the hyperaemic target. A sports ice pack will be placed on the skin surface of the knee corresponding to the area to be embolised, minimising non-target embolisation to cutaneous branches by temporary vasoconstriction. The vessels will be embolised with 0.1–0.3 ml of embolic agent at a time to prune the abnormal vessels. The sham procedure will be identical to the GAE procedure, except that 2 ml heparinised 0.9% saline, instead of the embolic agent, will be slowly injected. Participants will be monitored for 4 h post-procedure.

Follow-up data will be collected at 1, 3, 6, 12, and 24 months post-randomisation (Table 2).

**Table 2 Tab2:** Participant timeline

Timepoint	Study period														
	Enrolment	Allocation and treatment		Post-allocation						Post-treatment crossover to GAE after unblinding					

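### The tested VAS analysis may switch, on an undefined outcome-dependent trigger, to a logistic model of VAS = 0 versus above 0, which changes the question and can cost power or inflate false positives

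*Protocol article*

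**What the plan says.** - **Status of the endpoint.** The section Secondary Outcomes with Hypothesis Testing names two outcomes. One is pain relief, defined as "VAS change through 6 months post-randomisation".
- **Main analysis.** Under Statistics, Endpoints: "6-month VAS will be compared between GAE and sham treatment arms in an ANCOVA model", with arm and baseline pain score as the model terms.
- **Fallback.** The next sentence reads "Should the VAS be generally low, score will be dichotomised to with" and sets the two classes as a score above 0 and a score of exactly 0; then "a logistic regression analysis will be performed". Covariates for that model are not given.
- **Entry criterion.** Under Pain, Function, and Quality of Life Assessment, on the 0-100 scale: "This will be performed at baseline, with participants with a VAS" below 50 excluded. Table 1 agrees.
- **Unblinding.** Under GAE/Sham Procedure: "At 6 months post-randomisation, the participants and the study team will be unblinded". That is also the VAS endpoint visit. The Outcome Measures section keeps the staff who collate follow-up data blind to allocation.

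**The concern.** The fallback has three defects that need no calculation.

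1. **The trigger is open.** It rests on the 6-month VAS values, but no threshold, summary measure, pooled-or-by-arm basis or decision time is stated. Two analysts could both follow the sentence and report different models.
2. **The estimand changes.** With baseline in the model, ANCOVA of the 6-month score gives the same arm effect as ANCOVA of the change, so it matches the listed outcome. The logistic model estimates something else: the odds of having no pain at all.
3. **The cut suits this population poorly.** Everyone enters at 50 or more. A participant who goes from 80 to 1 is coded like one who stays at 80.

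At stake is the interpretability of one of the two outcomes listed for testing. Depending on how the choice is made and what form the benefit takes, its power and its type I error are at stake too.

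**Working it through.** **1. The plan's own figure.** The article gives no SD, effect or power for VAS. For KOOS4 it gives "a mean difference of 6.4 (i.e. effect size) between GAE and sham treatments", SD 10, and "an alpha error of 2-sided 0.05, and a power of 0.85".

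n per arm = 2(z₀.₉₇₅ + z₀.₈₅)² × SD² / difference² = 2 × (1.960 + 1.036)² × 100 / 40.96 = 43.8, so 44 per arm and 88 in total. Dropout: 88 / (1 − 0.20) = 110. Both figures reproduce; power at 44 per arm is 0.851.

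**2. Inputs for VAS.** From the article: 44 per arm, two-sided 0.05, baseline at least 50, scale 0-100. Assumed: baseline mean about 68; latent 6-month VAS normal with SD 22, floored at 0; correlation with baseline 0.3; effect 0.64 SD borrowed from KOOS4 (0.64 × 22 = 14.08 points). Each scenario has 4,000 simulated trials. Both models adjust for baseline, and the logistic test is a likelihood-ratio test.

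**3. Power under a shift in VAS.**

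| Latent sham mean | Zeros, sham / GAE | ANCOVA | Logistic | Loss (points) |
|---|---|---|---|---|
| 40 | 4% / 12% | 0.860 | 0.381 | 48 |
| 30 | 9% / 24% | 0.857 | 0.519 | 34 |
| 20 | 19% / 40% | 0.824 | 0.642 | 18 |
| 10 | 33% / 58% | 0.764 | 0.688 | 8 |

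The fallback is meant for low scores, so the lower rows matter most. With SD 20 and latent sham means of 5-20, ANCOVA has about 73-83% power and the logistic model 60-72%, a loss of about 2 to 22 points.

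**4. Power when the benefit takes another form** (a point mass at zero plus a gamma distribution above it).

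| Benefit | ANCOVA | Logistic |
|---|---|---|
| More zeros only, 30% v 60% | 0.51 | 0.82 |
| More zeros only, 10% v 35% | 0.35 | 0.83 |
| 8 points lower among those still in pain, zeros 30% in both arms | 0.39 | 0.06 |
| The same, zeros 10% in both arms | 0.59 | 0.06 |

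**5. Type I error, no true effect, SD 22.**

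| Zeros | ANCOVA | Logistic alone | Switch on pooled mean | More favourable test picked |
|---|---|---|---|---|
| 4% | 0.044 | 0.089 | 0.071 | 0.126 |
| 9% | 0.048 | 0.074 | 0.056 | 0.112 |
| 19% | 0.048 | 0.054 | 0.049 | 0.088 |
| 33% | 0.051 | 0.053 | 0.060 | 0.090 |

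With SD 20 and a switch when the pooled mean is below 20 (an illustrative cut-off), the rate is about 4.5-6.5%. Picking the favourable test gives about 9-11%. For comparison, two independent tests at 0.05 give 1 − 0.95² = 0.0975. The top row is inflated by the logistic test itself, which is unreliable when zeros are sparse.

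**6. Does the floor force a switch?** No, in these scenarios. ANCOVA holds its level at 0.044-0.051 even with a third of scores at zero.

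**The case against.** **Inflated type I error is not established.** A reader might infer that the switch inflates false positives as a matter of course. The text does not support that: it ties the switch to the level of VAS, not to p-values or arm differences, and a trigger on pooled data leaves the rate near 5-6%. The 9-11% needs a choice made with sight of the arm results. Unblinding the study team at 6 months leaves room for that, and no stated rule excludes it, but nothing says it is intended. This objection stands, so the claim is that the rule can inflate error.

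**The largest power losses lie where the rule would hardly apply.** A sham mean of 30 or 40 is difficult to call low, and at a latent mean of 10 the loss is 8 points. The ranking reverses if the benefit is mainly complete pain freedom. This stands as well; losses of 34 or 48 points should not be quoted as the expected cost.

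**A pile-up at zero is a recognised reason for another model.** True, but a rank-based or ordinal model handles it without discarding every distinction above zero.

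**The contingency may be remote.** With entry VAS of at least 50, many exact zeros at 6 months look unlikely. That is a judgement, and it lowers the severity without repairing the rule.

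**An analysis plan may supply the threshold.** It may, and a missing threshold alone would be no finding in a condensed article. But the article itself fixes an outcome-dependent switch and a cut at zero. Defining the trigger elsewhere would not undo the change of estimand.

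**Conclusion.** The point holds at moderate severity. The article states an outcome-dependent rule with an undefined trigger that changes both the model and the estimand of a tested secondary outcome. This follows from the text alone.

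The size of the consequences is conditional. Under a 0.64 SD shift and plausibly low VAS, the logistic model gives up about 2 to 22 points of power; under a benefit confined to more exact zeros it gains power. False positives reach about 9-11% only if the analysis is chosen knowing the arm results. These figures rest on assumed VAS means, SDs, baseline correlation and distributional form, and on an effect size borrowed from KOOS4.

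A reader might go further and conclude that the trial's main efficacy result is at risk. It is not: the KOOS4 analysis and its sample size do not depend on this rule.

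**What to change.** Delete the dichotomisation sentence. State that ANCOVA of 6-month VAS on arm and baseline VAS is the only tested VAS analysis, whatever the distribution of scores. Prespecify a rank-based ANCOVA or a proportional-odds model as the sensitivity analysis for floor effects, and report the share with VAS = 0 by arm descriptively.

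If the sponsor wishes to keep a switch, the second-best option is a numerical trigger on pooled data, applied blind to arm and fixed before unblinding. That keeps the error rate near nominal but leaves the change of estimand in place.

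The cost is wording only: no new data, visits or participants. The one downside is lower power than the logistic model if the true effect is mainly on complete pain freedom.
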